### Ethical considerations and regulatory approval

There are no immediate ethical problems regarding this trial. Research has not identified any significant adverse effects or risks from any of the compared interventions, and we have no advance knowledge of which intervention is most efficacious. During the trial period, any adverse event will be reported.

The trial is approved by the Regional Ethics Committee of Zealand (no: SJ-371), and is registered at the Danish Data Protection Agency (no: REG-55-2014). The trial is registered under Clinical Trials.org as NCT02068326. In accordance with the CONSORT guidelines [101, 102], we will report positive, negative, and neutral findings in the trial and we have completed the SPIRIT 2013 checklist (please see Additional file 1) and figure (please see Additional file 2).

### Confidentiality

All study-related information will be stored securely at the study site. All participant information will be stored in locked file cabinets in areas with limited access. All data will be identified by a coded identification number only to maintain participant confidentiality. All records that contain names of other personal identifiers such as locator forms and informed consent forms will be stored separately from study records identified by code number.

### Protocol amendments

Any modifications to the protocol, which may affect the conduct of the study, including changes of study objectives, study design, patient population, sample sizes, or study procedures, will require a formal amendment to the protocol. Such amendments will be registered at https://clinicaltrials.gov/ct2/show/NCT02068326 and approved by the ethics committee.

## Discussion

BPD typically emerges in adolescence and the recommended primary treatment is psychotherapeutic programs. However, only recently has research begun to investigate essential questions such as the relative effectiveness of separate program components and which level of specialization versus generalist treatment is needed for treatment of adolescent BPD to be successful [103]. The evidence base for cost-effective treatment programs for adolescent BPD is limited.

This is the first randomized controlled trial to test the efficacy of a MBT in groups for adolescents with BPD or subthreshold BPD. Below, we discuss some of the potential limitations and strengths of the M-GAB trial.

The trial is subject to at least three potential limitations. First, our primary outcome measure, the BPFS-C, was selected because it reliably and validly measures borderline personality features *specifically* in adolescents (rather than in adults) and has shown to be a sensitive outcome measure for adolescents in a previous randomized trial [53]. However, although patient-reported outcomes have obvious benefits [104], they are not observer blinded and therefore at risk of being assessed with some bias. In our trial, patients allocated to MBT may be biased by their knowledge of having received a relatively specific psychotherapeutic treatment and therefore be more optimistic about their outcome. In response to this potential limitation, we included an observer rated measure of change in BPD symptoms, the ZAN-BPD [88], as a secondary outcome.

Second, no standardizations for treatment of adolescent BPD pre-existed within the child and adolescent department, Region Zealand and for the purpose of this study, the limit for the minimum treatment in the TAU arm was defined as 12 monthly individual sessions. Individual treatment allows therapists to focus more intensely on the patient compared to group-based treatment and therapists in the TAU arm may choose to deliver treatment to some patients with a higher frequency than once a month. However, this does not completely rule out the risk of a dose–response effect since MBT is delivered on a weekly basis. We defined the minimum frequency for TAU treatment in order to minimize the possible effect of dose–response, but as completely equal doses of treatment in the two treatment arms is not guaranteed, the risk is not completely ruled out. We will monitor and register both the MBT and TAU patients’ contact to the health system during the treatment period, to be able to report on any differences in the treatment doses received.

Third, the MBT therapists are trained and supervised by engaged and specialized supervisors in a specific treatment model. It is possible that, as the supervisors believe in the advantages of the MBT model, this may influence the therapist allegiance. We were aware of the potential allegiance bias when designing the trial, but wanted to ensure therapist adherence to treatment model. The alternative of having less training or less specialized supervisors increases the risk of therapists not being adherent to the treatment model, which we considered an even greater risk to the trial.

We would also like to emphasize at least three possible strengths of the trial. First, we included borderline severity as a stratification variable in order to minimize the risk of confounding our findings by an unbalanced distribution of patients with BPD at the threshold versus subthreshold level. Second, we included outcome measures relying on different methods and sources of data (self-report, parental reports, observer-rated interviews and expert ratings) and covering different aspects of quality of life such as symptomatic improvement and social functioning. By including multiple outcome measures, we hope to be able to discuss outcome in broader terms. Third, in the selection of in- and exclusion criteria we aimed for participants to be as close to patients with BPD or subthreshold BPD typically referred to treatment at Child and Adolescent Psychiatric Department, Region Zealand. For example, patients living with foster parents or other kinds of parental substitutes and patients presenting comorbidity or substance abuse were included. Accordingly, the findings of the trial should have a wide generalizability.

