### Assessment and instruments

#### Diagnostic evaluation at baseline

Baseline assessment will be carried out prior to randomization by the first author and a research assistant, both of whom are clinical psychologists. The first author will not carry out treatment in any of the treatment arms. The research assistant may deliver MBT-I to smaller groups of patients. He or she will not deliver TAU.

*Clinical syndromes:* general psychopathology will be assessed with the Mini-International Neuropsychiatric Interview for children and adolescents (MINI-KID 6.0) [69], which is a structured diagnostic interview for children aged between 6 and 17 years old based on 24 DSM-IV and ICD-10 criteria. The MINI-KID generates reliable and valid psychiatric diagnoses for children and adolescents [70].

*Personality disorders* will be assessed with the Structured Clinical Interview for DSM-IV-Axis II (SCID-II) [71]. SCID-II assesses the presence of personality disorders listed in the DSM-5. The SCID-II is considered the “gold-standard” assessment instrument for personality disorders [72], and has shown good psychometric properties [71]. All SCID-II interviews will be carried out by the first author who is a trained and experienced SCID-II interviewer.

*Borderline personality disorder.* Zanarini et al.’s [73] Childhood Interview for DSM-IV Borderline Personality Disorder (CI-BPD) was developed to also allow the identification of subthreshold borderline pathology in children. The CI-BPD is a semi-structured interview in which the interviewer asks a series of questions and subsequently rates each DSM-based criterion on a score of 0 (absent), 1 (probably present) or 2 (definitely present). The CI-BPD has excellent psychometric properties [73, 74] and has demonstrated significant, albeit moderate, agreement to clinician diagnosis at time of discharge in a sample of inpatients (kappa = .47) and good internal consistency with a Cronbach’s alpha of 0.82 [75]. The first author has been trained in the CI-BPD by Zanarini in person and will train all other assessors in the study to secure good inter-rater reliability.

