### Outcomes

#### Primary outcome

The primary outcome, the Borderline Personality Features Scale for Children (BPFS-C) [76], is a 24-item dimensional measure adapted from the borderline scale of the Personality Assessment Inventory (PAI) [77] for use with children and adolescents from 9 years of age. It has the same four subscales as the PAI borderline scale: Negative Relationships, Affective Instability, Self-harm and Identity Problems. The 24 items are rated on a 5-point Likert scale, ranging from 1 (not at all true) to 5 (always true) with a higher total score indicating more severe levels of borderline personality features. Crick et al. [76] established evidence for the construct validity and demonstrated high internal consistency. Evidence for cross-informant concordance, criterion and concurrent validity were established by Sharp and colleagues [78]. Satisfactory construct and criterion validity has also been found for the abbreviated 11-item version of the BPFS-C [79]. In an RCT of individual MBT for adolescents [53], the BPFS-C was found to be sensitive to clinical change.

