### Randomization, methods to minimize bias, and blinding

In order to keep assessors blind to the patients’ treatment allocation, all pretreatment assessments will be carried out prior to randomization. Randomization to either MBT or TAU are done online by the trial coordinator (the first author) using a stratified block randomization procedure with a computer-generated allocation sequence with a varying block size kept unknown to the investigators by Public Health and Quality Improvement Data Management*.* Stratification will be according to clinic affiliation and borderline severity, that is, scores on the BPFS-C. More stratification variables are relevant (i.e., socioeconomic status), but not possible to apply due to the small number of participants. Patients randomized to the MBT will initiate the individual case formulation sessions (see Fig. 1) prior to MBT-I, and thereby will initiate the treatment program immediately. Patients randomized to TAU are allocated to a therapist and begin individual sessions immediately.

Assessments during the treatment phase are limited to self-report measures, hence no blinding will be possible. All information given to the participants before completing the self-reports will be standardized.

Regarding outcome assessments at discharge, we will minimize bias that knowledge of treatment allocation could cause by implementing the following strategies: (a) outcome assessors will be blind to treatment allocation, (b) outcome assessors and therapists will not directly communicate with each other, and (c) patients are asked not to reveal their treatment allocation during outcome assessments. Furthermore, outcome assessors will be asked to guess the patients’ treatment allocation so that the effects of possible bias can be examined in the analysis and all outcome assessor interviews will be recorded and a random sample will be re-rated by independent raters. Outcome assessors will be research assistants or clinical psychologists, who have not been trained in MBT, have not been involved in delivering treatment to participating patients, and have not carried out any intake procedures, including baseline assessments. The statistician will perform statistical analyses with the two intervention groups coded as ‘A’ and ‘B’, with randomly chosen therapist identifications.

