### Data management and statistical approach

Data-management will be handled by Public Health and Quality Improvement Data Management from Central Denmark Region, Aarhus. They will provide support with randomization, set up questionnaires electronically and will keep the data on their secure servers. Hence, none of the staff members involved in the study will have access to outcome data during the treatment phase.

All analyses will be conducted according to the ITT principle. Characteristics of the treatment groups will be described at baseline. Preliminary analysis will investigate the pattern of missingness at follow-up, and multiple imputation will be used for missing values. The primary outcome is the total score of the BPFS-C, which is treated as a continuous, normally distributed variable. The primary efficacy hypothesis will be tested using a multilevel two-group comparison (MBT vs. TAU), with Group as a main effect, Therapy Group as a random intercept (within the MBT group, see, e.g., [96]), the prerandomization BPFS-C as a continuous covariate and the stratification factor clinic as categorical covariate. The test will be performed at the 5 % two-tailed significance level. The primary test for efficacy will be based on the intention-to-treat population, with all randomized patients entering the analysis set, and multiple imputation of missing values. The result will be expressed as the covariate-adjusted difference in group averages, along with the two-sided 95 % confidence interval.

For the secondary outcomes, similar analyses will be used, taking into consideration the scale of the variable (e.g., logistic regression for binary outcomes). A sensitivity analysis will be based on the per protocol set for the available cases (without imputation). Linear regression and logistic regression analyses will be conducted to examine the predictive power of the different covariates (i.e., personality pathology, mentalizing, and attachment) on treatment efficacy and treatment completion.

We will use multiple imputations for missing values in the primary and secondary outcomes [97]. Separate imputation models will be used for the two treatment groups [98]. The imputation models will include the primary and secondary endpoints (baseline and follow-up) as well as the covariates of the primary statistical analysis, and therapist time in hours.

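### Stratifying on BPFS-C score protects only weakly against the threshold/subthreshold imbalance named as its purpose, and the primary model does not adjust for diagnostic level

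*Protocol article*

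**What the plan says.** Under Discussion, the first of the listed possible strengths is that "we included borderline severity as a stratification variable in order to minimize the risk of confounding our findings by an unbalanced distribution of patients". The risk meant there is an "unbalanced distribution of patients with BPD at the threshold versus subthreshold level".

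The section on randomization and blinding defines the factor: "Stratification will be according to clinic affiliation and borderline severity, that is, scores on the BPFS-C". It adds that other stratification variables are relevant, "but not possible to apply due to the small number of participants".

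The section on data management and statistical approach specifies the primary model: treatment group as main effect, therapy group as a random intercept within the MBT arm, "the prerandomization BPFS-C as a continuous covariate and the stratification factor clinic as categorical covariate".

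The eligibility criteria require at least four DSM-5 BPD criteria and, separately, a BPFS-C total above 67. Under the baseline diagnostic evaluation, the CI-BPD is the interview that "was developed to also allow the identification of subthreshold borderline pathology in children". It rates each criterion 0, 1 or 2. The SCID-II is also given at baseline. The BPFS-C is described as a 24-item dimensional scale with items scored 1 to 5.

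**The concern.** The protocol names one variable as the risk and stratifies on another. Whether a patient is at or below the diagnostic threshold depends on how many criteria an interviewer rates as met. The stratum is a questionnaire total that every patient, at either level, must already have above the clinical cutoff, so that cutoff cannot separate the two levels. Diagnostic level is absent from both the randomization factors and the covariates of the primary model.

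Two things are at stake. A reader would credit the design with a balance that it delivers only in small part. And a baseline variable that the protocol itself treats as a possible confounder, and collects before randomization, is not used in the main comparison.

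**Working it through.** The plan gives no figure for the protection it claims, so there is none to reproduce. Its sample-size inputs supply the scale: a 12-point target, SD 15.4, and 112 patients at 1:1, hence 56 per arm. A two-sample t-test at 90% power and 5% two-sided gives 35.6, rounded up to 36 per arm, which reproduces the stated 72 before inflation.

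**Step 1. Chance imbalance with no balancing on severity.** The threshold share p is not given; 70% is assumed, range 60 to 80%. The SD of the difference in shares is sqrt(2p(1−p)/56).
- p = 0.6: sqrt(0.48/56) = 9.3 percentage points
- p = 0.7: sqrt(0.42/56) = 8.7
- p = 0.8: sqrt(0.32/56) = 7.6

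At p = 0.7, the chance of a gap above 15 points is 2 × (1 − Φ(0.15/0.0866)) = 8.3%.

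**Step 2. What BPFS-C strata add.** Stratified permuted-block allocation was simulated with 112 patients, four clinics, a median split of BPFS-C and blocks of 2 or 4. The split, the block sizes and the latent correlation between BPFS-C and diagnosis are all assumptions. SD of the between-arm difference in threshold share, in percentage points:

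| Threshold share | Clinic only | BPFS-C strata, r = 0.3 | r = 0.5 | r = 0.7 | Strata on diagnosis |
|---|---|---|---|---|---|
| 50% | 9.4 | 9.4 | 9.1 | 8.2 | 2.2 |
| 70% | 8.7 | 8.4 | 8.2 | 7.8 | 2.3 |
| 85% | 6.7 | 6.7 | 6.5 | 6.3 | 2.6 |

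At a 70% share, the chance of a gap above 10 points is 25% with clinic strata only, 20 to 23% with BPFS-C strata at r = 0.7 to 0.3, and about 0% with strata on diagnosis. By the normal approximation of step 1, a gap above 15 points has a chance of 5.3% (SD 7.8) to 7.4% (SD 8.4). Even at r = 0.7, BPFS-C strata remove only about a tenth of the SD: 1 − 7.8/8.7 = 10%.

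**Step 3. Effect on the primary estimate.** The shift is the gap times b, where b is the difference in discharge BPFS-C between threshold and subthreshold patients at equal baseline BPFS-C. The documents do not give b; 5 points is assumed, with half and double shown. The unadjusted standard error is 15.4 × sqrt(2/56) = 2.91 points. Clustering would raise it and baseline adjustment would lower it.
- 15-point gap, b = 5: 0.15 × 5 = 0.75 points, which is 0.26 SE and 6% of the 12-point target
- 15-point gap, b = 2.5: 0.38 points (0.13 SE); b = 10: 1.5 points (0.52 SE)
- One SD of imbalance (8.2 points, r = 0.5), b = 5: 0.082 × 5 = 0.41 points (0.14 SE)
- For a 15-point gap to shift the estimate by one SE, b would have to be 2.91/0.15 = 19.4 points, more than the outcome SD

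**Step 4. Precision that adjustment could recover.** With b = 5 and p = 0.7, diagnostic level accounts for roughly 25 × 0.21 = 5.25 of a variance of 15.4² = 237, about 2%, so the SE would fall by about 1%. With b = 10 it accounts for 21/237 = 9%, and the SE would fall by about 5%. Both are rough, because the variance left after baseline adjustment is smaller than 237.

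**The case against.** The strongest reply is that the Discussion promises little. It speaks of possible strengths and of minimizing a risk, not of guaranteed balance. The article reports criterion and concurrent validity for the BPFS-C, so some association with diagnosis is plausible. Totals run from 24 to 120, so entry above 67 still leaves 68 to 120, more than half the scale. The outcome's own baseline is a continuous covariate, so diagnostic level can move the estimate only through prognosis that baseline BPFS-C does not carry. Adjusting for baseline outcome and clinic is a standard choice.

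All of this stands, and it limits the point. A reader might infer that the stratification gives no protection, or that the primary comparison is biased. The documents support neither. They give no correlation between BPFS-C and diagnosis, so zero protection cannot be asserted. Any imbalance under randomization is by chance, and the test and confidence interval already allow for it.

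Two further replies help less. Baseline secondary endpoints, including the ZAN-BPD, enter the imputation: "The imputation models will include the primary and secondary endpoints (baseline and follow-up) as well as the covariates of the primary statistical analysis". Personality pathology is also a predictor in separate regressions. Neither adjusts the primary comparison. The small sample is a reason against more strata, but not against one further covariate.

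**Conclusion.** The point holds as a mismatch between a stated design strength and the methods. Stratification and the baseline covariate address BPFS-C severity directly and diagnostic level only indirectly. On the assumed inputs, BPFS-C strata reduce the SD of threshold/subthreshold imbalance by about a tenth at most for a 70% threshold share (13% at a 50% share, 1 − 8.2/9.4), against about three quarters when stratifying on diagnosis itself (1 − 2.3/8.7 = 74%).

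The consequence for the primary result is small: 0.4 to 0.75 points at b = 5, and about half a standard error in the least favourable case shown. The primary test is valid and the sample size is unaffected. These sizes rest on an assumed threshold share, correlation, BPFS-C split and residual prognostic difference, none of which is in the document. The mismatch rests on the text alone. The change is worth making because it is nearly free and makes the plan do what it says it does.

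**What to change.** 1. Prespecify the baseline number of BPD criteria used for eligibility as a fixed covariate in the primary model or, failing that, in a named sensitivity analysis. A count is preferable to a yes/no split because the article defines no numerical cut between threshold and subthreshold.
2. State which interview supplies the count, since the CI-BPD and the SCID-II are both given at baseline. If it is the CI-BPD, state which ratings count as a criterion met.
3. Reword the Discussion sentence to say that stratification balances BPFS-C severity, while diagnostic level is handled by adjustment.

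No change to the randomization is needed. The data are collected before allocation, and the imputation models already take in whatever covariates the primary model has. Recruitment was under way at publication, and study staff have no access to outcome data during treatment, so the change can go through the protocol's amendment route without knowledge of results. The cost is one degree of freedom and one corrected sentence. If the criterion count adds no prognostic information beyond baseline BPFS-C, there will be little gain in precision.

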## Trial status

The trial is currently in the recruitment phase. The first patient was included and randomized on 24 September 2015 and inclusion is expected to be completed in January 2017.

## Abbreviations

M-GAB, Mentalization-Based Treatment in Groups for Adolescents with Borderline Personality Disorder (BPD) or subthreshold BPD versus Treatment As Usual; BDI-Y, Becks Depression Inventory for Youth; BPD, borderline personality disorder; BPFS-C, Borderline Personality Features Scale for Children; BPFS-C-11, Borderline Personality Features Scale for Children-Short version; BPFS-P, Borderline Personality Features Scale for Children-Parents’ version; CAT, cognitive analytic therapy; CBCL, Childhood Behavior Checklist; C-GAS, Children's Global Assessment Scale; CI-BPD, Childhood Interview for DSM-IV Borderline Personality Disorder; DBT, dialectical behavior therapy; DSM-5, *Diagnostic and Statistical Manual of Mental Disorders, fifth edition*; ECR, Experience of Close Relationships Inventory; IPPA-R, Inventory of Parent and Peer Attachment-Revised; ITT, intention to treat; MINI-KID, Mini International Neuropsychiatric Interview for children and adolescents; MBT, mentalization-based treatment; MBT-G, mentalization-based treatment in groups; MBT-I, mentalization-based treatment-introduction; MGT-P, mentalization-based psychoeducation therapy for parents of patients; PAI, Personality Assessment Inventory; PD, personality disorder; RCT, randomized controlled trial; RFQ-Y, Reflective Function Questionnaire for Youth; RTSHIA, Risk-Taking and Self-Harm Inventory for adolescents; SCID-II, Structured Clinical Interview for DSM-IV-Axis II; TAU, treatment as usual; YSR, The Youth Self-Report; ZAN-BPD, Zanarini Rating Scale for Borderline Personality Disorder
